### Preliminary Research

The intervention components were chosen based on the findings from a qualitative study [7] conducted in Azerbaijan from 2014 to 2016 with children aged 8 to 16 years who had a history of institutionalization and their caregivers (n=47). In-depth interviews were conducted with children, caregivers, and experts working with these families. Three primary areas for intervention were identified: addressing children’s mental health needs, strengthening family relationships, and tackling financial challenges during reunification [21,22].

A pilot feasibility study was carried out from 2017 to 2019 to adapt and pretest the family-strengthening intervention with 20 reunified families. The adapted intervention was pilot-tested in partnership with 2 local organizations: SOS Children’s Villages-Azerbaijan (community-based service provider) and the National Mental Health Centre (NMHC; research and delivery of mental health services). This study uses an adapted version of SAFE Children, a family-based preventive intervention originally developed and tested in the United States for at-risk families in low-income urban neighborhoods [23]. SAFE Children was selected because of its strong strengths-based approach and its demonstrated acceptability to families of varying sizes and compositions—a critical feature when working with families affected by institutional care, many of whom do not live in traditional 2-parent households. The research team adapted SAFE Children to the cultural context of Azerbaijan and trained 10 local facilitators (eg, social workers, family support workers) to deliver the adapted version, named “Bütöv Ailə” (Families Together in Azerbaijani). The program consists of 12 weekly multifamily group sessions focused on improving parent-child relationships, supportive parenting practices, communication skills, and child behavior management, with additional content addressing unique challenges faced by families during reunification after institutional care (eg, stigma, fear of abandonment).

### Theoretical Framework

The study is informed by theories of family resilience [24,25] and emotional regulation [26,27]. Developmental theory suggests that adversity and trauma experienced in early childhood may interfere with typical developmental trajectories, which can result in emotional and behavioral problems [28,29]. Yet, with appropriate resources and support, children may develop resiliency and overcome disadvantages [30,31]. In addition, asset theory [32] posits that assets—such as savings, homeownership, education (human capital), stable housing, and small business ownership—unlike cash benefits, which can be quickly depleted, provide significant long-term psychological benefits beyond economic outcomes, such as reducing financial stress and enhancing aspirations and hopes for the future [33,34].

Therefore, it is hypothesized that strengthening children’s individual capacities and external resources can balance the effects of adversity and improve mental health outcomes. Enhancing children’s coping skills, strengthening child-parent relationships, reducing parental stress, and improving family economic well-being by incentivizing savings and building assets will result in children demonstrating fewer symptoms of (1) internalizing problems (depressive or anxious mood), (2) externalizing problems (aggressive, delinquent, or disruptive behaviors), and (3) posttraumatic stress (Textbox 1).

Textbox 1.Conceptual model.
**Intervention components**
Trauma-focused mental health services (psychoeducation, attunement, coping, and self-regulation skills)Family strengthening intervention (multifamily groups on family communication, conflict resolution, and family support)Asset-based economic intervention (Matched Child Savings Accounts, financial education, and mentoring)
**Proximal mediators**
Emotion regulation (decreased parental distress, impulsivity)Positive family relations (supportive parenting, quality of child-parent and family relationship)Economic well-being (food security, household assets, housing, employment)
**Child mental health outcomes**
ConstructsCognitive and executive functioning (attention, cognitive control or inhibition, working memory)Social processes (emotion recognition, affiliation, and attachment)Clinical outcomesinternalizing problems (depressive, anxiety, trauma symptoms)externalizing problems (aggressive, antisocial, or delinquent behaviors)Functional outcomes (academic performance, peer relations)

### Intervention A: Family Strengthening

This study uses an adapted version of the family-strengthening intervention “SAFE Children” to improve child-parent relationships, enhance supportive parenting strategies, and prevent emotional and behavioral problems among at-risk children [23]. SAFE Children was initially designed for at-risk families from low-income US neighborhoods and uses a multi-family group approach to build social support. Including multiple families is an efficient service delivery model, fostering support among participants and improving parent-child interactions directly [35].

Families participated in 12 weekly sessions, with themes including identifying family strengths, developmental expectations, communication skills, behavior management, parental distress management, and conflict resolution. The adapted intervention incorporates topics that address unique issues faced by families during reunification (eg, attachment issues, children’s feelings of resentment, parental guilt, and shame). In response to the findings of the pilot study, sessions were offered on weekends to accommodate families’ schedules. The intervention developer and coinvestigator ([name]) oversaw the training and intervention adaptation process to ensure fidelity to its core components. The intervention is delivered in multifamily groups of 5 families. Children and caregivers attend sessions together, separating into child- and caregiver-specific activities only when required by the curriculum. To strengthen family engagement and reinforce skills at home, all household members involved in child-rearing are encouraged to participate, including siblings who do not meet study eligibility criteria.

### Intervention B: Mental Health Services

Families were connected to clinicians from the NMHC to receive child mental health services. Services included a clinical assessment performed by a psychiatrist, the development of an individual care plan, and assignment to a mental health clinician—typically a child psychologist—who provided services to the child and caregiver. The trauma-focused child mental health services were grounded in the Attachment, Regulation, and Competency framework [36]. All clinicians delivering this intervention received additional training in trauma-focused mental health approaches, including Attachment, Regulation, and Competency, and participated in biweekly group supervision delivered by a bilingual licensed psychologist from the United States. The clinicians delivering this intervention were not involved in conducting research activities. As a public entity, the NMHC provides all mental health services to the public free of charge. Children typically attended individual sessions once a week (30‐45 min), with parent or caregiver involvement incorporated as clinically indicated. Up to 12 sessions were offered; however, services could be extended based on individual treatment plans and clinical needs.

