## Methods

### Study Design

This randomized clinical trial used a full 2³ (2×2×2) factorial design based on the multiphase optimization strategy (MOST) framework to test and compare three intervention approaches: (1) a family-strengthening intervention, (2) trauma-focused child mental health services, and (3) asset-based economic empowerment via Child Development Accounts (CDAs).

Multicomponent interventions are often tested as “bundles,” making it difficult to disentangle the contributions of individual components. The MOST is a systematic method that allows for the testing of the independent effects of different intervention components to identify their most optimal combination [15]. While multiarm randomized controlled trials are costly, often limited in arms, and require larger sample sizes, the MOST uses a factorial design. By comparing combinations of experimental conditions, the study can have a greater number of conditions without a substantial increase in sample size. This is advantageous in LMICs, where it is essential to implement only the most efficacious aspects of a program. The MOST consists of three phases: (1) preparation, (2) optimization, and (3) evaluation of the optimized intervention in a randomized controlled trial [16]. This study falls within the optimization phase.

This study includes 3 factors—the intervention approaches—each with 2 levels (delivered/“on” or not delivered/“off”). This is a full 2×2×2 factorial design, meaning that the study has 8 different experimental conditions or groups (2^3^=8) [17]. Child-parent dyads (n=439) were randomly assigned to 1 of 8 groups (about 54 dyads per group), which determined the combination of interventions they received. Given this design, half of the sample (n≈220) received each intervention (eg, families assigned to groups 1‐4 received the family-strengthening intervention and were compared with families from groups 5‐8; Table 1).

**Table 1. T1:** Experimental conditions^a^.

Group	Usual care	Experimental interventions		
	Standard deinstitutionalization program	Family strengthening	Trauma-focused mental health services	Economic empowerment
1	On	On	On	On
2	On	On	On	Off
3	On	On	Off	On
4	On	On	Off	Off
5	On	Off	On	On
6	On	Off	On	Off
7	On	Off	Off	On
8	On	Off	Off	Off

a Child-parent dyads (n=439) are randomly assigned to 1 of 8 experimental conditions (~54 dyads per group), determining how many and which intervention components participants receive.

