Aim 1: To estimate the effects of intervention components on child mental health outcomes, differences in outcomes (eg, depression score) will be tested across 3 time points (baseline, 1 year, and 2 years), under an intent-to-treat basis, using linear mixed models. This approach accounts for the autocorrelation of observations nested within individuals over time. We will use logistic functions for binary outcomes (eg, mental health symptoms above the clinical cutoff), Poisson or negative binomial functions for count outcomes (eg, the number of aggressive behaviors), and linear functions for continuous variables (eg, self-esteem score). Statistical inference will be based on F-statistics and their associated *P* values for between-subject effects (the intervention assignment × time terms). To estimate the main effects for the 3 intervention components, we will determine if there is a difference in change across time using the baseline as the reference point (eg, 1 year vs baseline; 2 years vs baseline). We will also include 2-way interactions between components (eg, Family Strengthening by Economic Empowerment by Time interaction). Since we will use effect (–1, 1) coding rather than dummy (0, 1) coding, the power for tests of main effects and interactions will be identical for similarly sized effects. Covariates will include baseline attributes for outcome variables (eg, child’s age and gender, caregiver characteristics).Aim 2: To test which intervention component is mediated by hypothesized mediators, including (1) supportive parenting (eg, quality of child-parent relationships), (2) emotion regulation (eg, self-regulation), and (3) parental stress (eg, stress response). We will use a 2-step process [61] to test (1) a measurement model using confirmatory factor analysis that examines the relationships between the latent constructs and their indicator variables and (2) a structural model to test the hypothesized relationships between the latent mediating and outcome constructs and the intervention [62]. We will use the maximum likelihood method of parameter estimation with missing data. We will also conduct separate analyses to examine the effectiveness of intervention components in specific subgroups (eg, by gender).Aim 3: Qualitative analysis will be conducted in both Azerbaijani and English to explore barriers and facilitators to intervention participation and implementation. Bilingual investigators and 2 additional coders will independently review interview transcripts and conduct thematic analysis [63] and content analysis [64] using Dedoose [65]. Analyses will assess themes and concepts regarding participants’ and intervention facilitators’ perspectives on mental health needs, intervention engagement and acceptability, changes in family relationships and dynamics, and contextual and sociocultural factors influencing intervention delivery and outcomes.

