
In the data analysis, the primary outcomes include children’s mental health and socioemotional functioning. Secondary outcomes include cognitive and social processes associated with mental health, as well as functional outcomes related to academic performance and social functioning in the school setting. Specifically, primary mental health outcomes include child-reported depressive symptoms, posttraumatic stress symptoms, and self-esteem; caregiver- and teacher-reported ADHD symptoms and general socioemotional functioning such as internalizing and externalizing problems; and clinician-administered mental health outcomes among families randomized to the mental health services condition. Secondary outcomes include child cognitive functioning, assessed using WISC-V and CANTAB tasks; child-reported social support, particularly peer support; and teacher-reported grades and school behaviors. Mediating variables include caregiver-reported parenting practices, caregiver mental health, family functioning, coping strategies, social support, saving attitudes, and household economic well-being.

The main analyses focus on treatment effects at the 1-year and 2-year follow-ups, with the 1-year follow-up used to assess initial intervention effects and the 2-year follow-up used to assess the maintenance of those effects over time. Children from the same family will be accounted for using mixed-effects models, with random effects specified to adjust for the nonindependence of observations among children nested within the same family. Missing outcome data will be handled using maximum-likelihood estimation under a missing-at-random assumption, with sensitivity analyses using multiple imputation. To address the multiple testing issue, we will control the false discovery rate using the Benjamini-Hochberg procedure [66,67]. This approach was selected instead of Bonferroni correction because it limits false discoveries while avoiding the overly conservative loss of power associated with Bonferroni adjustment when multiple related hypotheses are tested.

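### Children given mental health services share clinicians, but the stated model has random effects for child and family only, so the B-by-time test is too liberal if outcomes correlate within clinician

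*Protocol article*

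**What the plan says.** Under Intervention B: Mental Health Services, the article says: "Families were connected to clinicians from the NMHC to receive child mental health services". The service includes "assignment to a mental health clinician", typically a child psychologist, and children usually attend weekly individual sessions. More than one clinician is involved: "All clinicians delivering this intervention received additional training in trauma-focused mental health approaches". Neither their number nor their caseload is given. Under Study Design, "half of the sample (n≈220) received each intervention". No clinician assignment is described for children with B off.

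The Analytical Strategy (Aim 1) uses linear mixed models for three time points and says of them: "This approach accounts for the autocorrelation of observations nested within individuals over time". Inference rests on the assignment-by-time terms, with baseline as the reference. For siblings, the same section plans "random effects specified to adjust for the nonindependence of observations among children nested within the same family". No random effect for clinician or delivery group is named.

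**The concern.** Children treated by the same clinician share that clinician's skill, style and adherence to the framework, so their changes after baseline may be correlated. This dependence exists only where B is on, which makes the design partially nested. A family effect does not capture it once a clinician sees more than one family.

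If the correlation is positive, the B main-effect-by-time test uses too small a standard error. Its interval is then too narrow and its p-value too small. Those p-values enter the Benjamini-Hochberg procedure, which relies on valid p-values, and the results feed the choice of intervention package, which is the purpose of this optimization trial.

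**Working it through.** **The plan's own figures.** Power Calculations starts from 400 children less 10%: 400 × 0.90 = 360, which agrees. It reports 80% power for effect sizes of 0.09 to 0.12 without naming the metric or the two autocorrelation values, so there is no unique reproduction. Read as Cohen's f for a between-group test with 2 groups, 3 visits and N = 360, the detectable f is 0.094 at an autocorrelation of 0.1 and 0.121 at 0.5. The range is therefore reachable, and I do not call it wrong. Autocorrelation is the only dependence the section mentions; this reproduction needs no clustering term.

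**Do caseloads span families?** The trial has 305 caregivers, so about 305/2 ≈ 152 families have B on. Caseloads stay within families only if there were close to 152 clinicians.

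**Inputs for the size**
- Children with B on: about 220 (Study Design).
- Number of clinicians J: not given; assumed 5, 10, 20 or 30, which is 44, 22, 11 or 7.3 children each.
- ICC: not given; assumed 0 to 0.10. Because the test concerns change from baseline, read it as the ICC of change.

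**Formulas**, with m = 220/J
- Design effect in the B-on half: DE = 1 + (m − 1) × ICC.
- B-off half: design effect 1.
- True SE / naive SE: R = √((1 + DE)/2).
- Actual two-sided error at nominal 5%: 2 × (1 − Φ(1.96/R)).

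Example, J = 10 and ICC 0.05: DE = 1 + 21 × 0.05 = 2.05; R = √(3.05/2) = 1.235; error = 2 × (1 − Φ(1.587)) = 11.2%.

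| Clinicians | ICC 0 | ICC 0.02 | ICC 0.05 | ICC 0.10 |
|---|---|---|---|---|
| 5 | 1.00; 5.0% | 1.20; 10.1% | 1.44; 17.4% | 1.78; 26.9% |
| 10 | 1.00; 5.0% | 1.10; 7.5% | 1.24; 11.2% | 1.43; 17.1% |
| 20 | 1.00; 5.0% | 1.05; 6.2% | 1.12; 8.0% | 1.23; 11.0% |
| 30 | 1.00; 5.0% | 1.03; 5.7% | 1.08; 6.9% | 1.15; 8.8% |

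Each cell shows R and the actual error. At the planned 180 analysed children per level the figures are slightly smaller (J = 10, ICC 0.05: 1.19 and 10.1%).

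A simulation with 305 families, 439 children and a family random effect in the fitted model agrees. At ICC 0.05 it gave R = 1.21 and 10.6% error with 10 clinicians, and 1.13 and 8.3% with 20. At ICC 0 the error was about 5%.

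With a correct SE, an effect powered at 80% under independence has power Φ((1.96 + 0.84)/1.235 − 1.96) ≈ 62% at J = 10, ICC 0.05.

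**Which clinician term matters.** Write the clinician effect as u. If u is the same at every visit, it drops out of follow-up minus baseline, and the B-by-time SE does not move. Take an assumed within-child variance of change of 0.90, 220 children per level, 10 clinicians and clinician variance 0.05:
- no clinician term, or a time-constant one: √(2 × 0.90/220) = 0.0905;
- clinician effect starting after baseline: √(2 × 0.90/220 + 0.05/10) = 0.1148.

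The ratio is 1.27. It is close to the 1.24 in the table but slightly higher, because the ICC of change here is 0.05/0.95 = 0.053 and 0.0905 leaves out the clinician variance altogether.

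**Components A and C.** For A, "The intervention is delivered in multifamily groups of 5 families", and the financial education in C also runs in groups of 5 families. At 439/305 = 1.44 children per caregiver, a group holds about 7.2 children. At ICC 0.05, R is 1.08 and the error about 6.8%. These groups are missing from the stated model too.

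**Not computed.** The effect on B's two-way interactions depends on how clinicians' caseloads fall across A and C, which is not stated.

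**The case against.** The strongest objection is that this is a condensed article, that the sentence on families explains how siblings are handled, and that therapist-level terms are often left to a statistical analysis plan. That plan may contain one. This limits the force of the point but does not remove it: the article states which dependence the model accounts for, and an analyst following it would fit no clinician effect although it describes clinicians as the delivery unit.

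Second, the driving inputs are assumed. This stands. A reader might infer that clinicians each treated many children and that the B standard errors are too small as a matter of fact. The documents support neither: caseload and ICC are not given, the error is nil at ICC 0, and it is small with 30 clinicians at ICC 0.02 (SE ratio 1.03, error 5.7%).

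Third, a reader might infer that the omission favours B over A and C when the package is chosen. The documents do not support this. The groups of 5 families for A and C are also unmodelled, and facilitators each deliver one type of intervention, so a facilitator's families may be correlated as well. Without cluster sizes and ICCs for all three components, no direction can be derived.

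Fourth, the design-effect formula is for two groups at one time point, whereas the planned test concerns change. This is met by reading the ICC as that of change. The simulation with a family effect gives similar figures.

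**Conclusion.** The point holds in conditional form. The stated random structure omits the unit through which B is delivered, and a family effect cannot stand in for it unless there were nearly as many clinicians as B-on families. If change correlates within clinician, B-by-time is tested against too small an error. Under the assumptions of 10 to 20 clinicians and an ICC of change of 0.02 to 0.05, the understatement is a factor of about 1.05 to 1.24, and the actual error rate is about 6% to 11%. It is larger with fewer clinicians or a higher ICC, and zero at ICC 0. No bias between components is claimed. The change is worth making, because the article reports that the intervention-effects analyses are still ongoing.

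**What to change.** For B-on children, add a partially nested clinician random effect that acts on post-baseline outcomes (clinician-by-time). A time-constant clinician intercept would leave the planned test unchanged. Use small-sample degrees of freedom for the B terms, such as Satterthwaite or Kenward-Roger, because the number of clinicians may be small. Say how B-on children who never met a clinician, or who changed clinician, are coded, so that the intent-to-treat set stays whole. Report the number of clinicians and the estimated ICC. Settle this before treatment effects are examined.

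First confirm that clinician identity can be obtained from the National Mental Health Centre's service records. The article's list of administrative data covers attendance, session completion, types of service and number of sessions, but not clinician identity.

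The cost is one more variance component, which will be imprecise if clinicians are few, a record merge, and somewhat wider intervals for B. If the ICC proves near zero, little is lost.

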### Intervention C: Asset-Based Economic Empowerment

#### Overview

The economic intervention involves 3 components: CDAs, financial education sessions, and monthly mentoring. Under Azerbaijan’s National Social Targeted Assistance Program, low-income families are eligible for small monthly cash allowances. While cash benefits provide immediate relief, they may not fully lift families out of poverty [37,38]. In contrast, CDAs encourage savings and asset investment (eg, a child’s education, housing, or small business development), aiming to prevent economic shocks, reduce poverty-related parental stress, and increase family stability [39,40].

